**Figure 2 Fig2:**
[figure not shown]
**Illustration of EMG electrode placement (A) and example EMG and motion signals (B).** Root-mean-square (RMS) EMG data and motion data are scaled according to the maximum of RMS EMG data **(B)**. B contains 3 cycles of flexion (B1), holding in position while fully flexed (B2), and extension (B3).

Participants are instructed to place their feet shoulder width apart with their arms hanging loosely at their side. Keeping their knees straight, they bend forward as far as they can and hold that position for 3 seconds, then return to the upright standing position. Participants perform this movement once as practice and to allow research personnel to ensure proper functioning of the system. The participant then performs the procedure 3 times in a continuous manner while the EMG and motion data are collected.

*Data reduction*: In order to quantify the degree to which the FRP is present, two different forms of a flexion-relaxation ratio (FRR) are used
[31, 32]. One is calculated by dividing the maximum root mean square (RMS) EMG activity level during flexion (while bending forward) by the lowest mean EMG activity as measured over a one second interval during the fully flexed phase. Another FRR is similarly calculated by dividing the maximum RMS EMG activity level during extension (while returning to standing erect) by the same minimum. The beginning and end of the fully flexed phase for each cycle are determined from the plot of the motion data. A macro written in Visual Basic for Applications, within Microsoft Excel (Microsoft Corp., Redmond, WA), is used to identify the specific regions of the data plots. These are regions of full flexion, the regions in which the trunk is flexing forward, and the regions in which the trunk is extending while returning to the upright position. The macro allows the user to adjust the limits of the various regions of the plot in order to exclude occasional spurious spikes in the RMS EMG data.

In all, 12 FRRs are calculated each time the participant performs this test. A set of 3 FRRs is based on the maximum RMS EMG activity during flexion – 1 FRR for each of the 3 cycles from the left paraspinal muscles. Another set of 3 is made from the right paraspinal muscles. Similarly, 2 more sets of 3 are made: one based on the maximum RMS EMG activity levels during extension from the left and the other similarly from the right paraspinal muscles. The FRRs for the 3 cycles of each situation are averaged which yields 4 mean FRRs each time a participant performs this activity: a mean FRR from flexion and one from extension for the left and right side. Once the regions have been identified the macro performs the necessary calculations.

### Secondary outcome measures

#### DC self-reported record of SM delivery over the course of treatment

DCs report all HVLA-SM delivered using a record log as illustrated in Figure 
3. This information will allow us to better identify SM delivery patterns from the clinical perspective.

**Figure 3 Fig3:**
[figure not shown]
**Self-reported record for high velocity, low amplitude spinal manipulation.** Level: the segment over which the manual contact occurs (L1-5, sacrum, and sacroiliac joint); Side Up: side of body contacted by clinician providing trunk twist motion direction; Contact Point: manual contact of the thrusting hand; SP: spinous process; MP: mammillary process; DW: interspinous space 1 cm lateral to spinous processes; PSIS: posterior superior iliac spine; Ischial Tubes: Ischial tuberosity; Fossa: midpoint between ischial tuberosity and PSIS; Base: Medial aspect of the superior sacrum; Apex: inferior sacrum; Ala: sacral ala or lateral superior sacrum; Direction of thrust: direction of thrust applied by the thrusting hand; A: anterior; S: superior; I: inferior; M: medial; L: lateral.

#### Contact force at the clinician’s thrusting hand

The measurement of contact force characteristics occurs as a part of the dynamic stiffness assessment (see more details below). The data reduction program used for segmental load is applied to extract variables from the contact force as measured under the clinician’s thrusting hand. These variables include the force exerted during the preload phase before the HVLA thrust, the loading rate, and peak force.

#### Segmental load

The method for estimating lumbar spine segmental load proposed by Triano and Schultz
[50] and Triano et al.
[51] was adapted for use in the current study with two modifications. Rather than using a rigid chest panel to limit the participant’s upper body movement, we stabilize the upper shoulder with a shoulder strap crossed behind the participant (Figure 
4). The strap restricts the predominant motion of the participants receiving HVLA-SM, which tends to include whole-body movement in the cephalic direction and a rolling movement of the lower trunk toward the clinician. The strap design attempts to mimic the clinician’s stabilization hand (non-thrusting hand). The strap is then secured to the force plate right under the participant’s thoracic cage such that force and moment occurring during the HVLA-SM procedure are monitored. The clinician’s non-thrusting hand is placed on a moveable rest located near but not touching the participants shoulder to approximate the typical position attained during the procedure and to help the clinician maintain balance (Figure 
4). The location of the lumbar segment targeted by the contact hand is traced with three Optotrak smart marker rigid bodies during the HVLA-SM procedure instead of the one-time digitization during the preload phase used by Triano et al.
[51]. As a result, it is possible to compensate for the effect that lumbar spine movement may have on segmental load.

**Figure 4 Fig4:**
[figure not shown]
**Illustration of segmental load assessment during side-lying high-velocity spinal manipulation.**

The method described in Triano and Schultz
[50] and Triano et al.
[51], however, does not consider the effect of lumbar segment orientation on segmental load. As a result, only the magnitude of the segmental force and moment will be reported. To estimate three-dimensional segmental load, the location of the joint center and its orientation of the target lumbar segment need to be determined. We adopted the method developed by Splittstoesser
[61] to fulfill this task. The procedure involves the creation of individualized lumbar spine models in the standing posture using skin marks over key spinal landmarks
[62]. Additionally four Optotrak smart marker rigid bodies are placed at C7, T7, T10, and S1 to estimate the orientation of the target segment using the individualized lumbar spine model (Figure 
4)
[61]. The limitation of Splittstoesser’s method is that it is only designed to estimate sagittal plane motion. It does not account for lumbar spine axial rotation or lateral flexion, which may also occur during HVLA-SM. Thus, investigation of the effects of segment orientation on segmental load estimation in this study is exploratory.

*Data reduction*: A custom-written MATLAB program is applied for segmental load data reduction. Variables extracted from the segmental load data include the force and moment during the preload phase of the HVLA-SM, loading rate, and peak force and moment.

#### Dynamic stiffness

To investigate dynamic spinal stiffness (i.e. the displacement, acceleration and force characteristics in time), a mixed approach is applied to measure: the movement of the doctor’s thrusting hand using a triaxial accelerometer (Model 356A17, PCB Piezotronics Inc., Depew, NY) with a sampling rate at 1000 Hz; the Optotrak motion capture system with a sampling rate at 100 Hz; and the arithmetic summation of the thrusting force over the area at the base of the palm using a thin pressure pad (Pliance system, Novel Electronics, St Paul, MN) with a sampling rate of 50 Hz. Our previous study demonstrated that a sampling rate at 50 Hz is sufficient for acquiring contact force during HVLA-SM
[36]. Two characteristics of dynamic spinal stiffness are computed using the force/displacement/acceleration-time profiles: 1) apparent mass (M) that takes into account the force applied (F) and the resulting acceleration (a) of the contact interface (M = F/a); and 2) driving-point mechanical impedance (Z) that takes into account the force applied (F) and the resulting velocity (v) of the contact interface (Z = F/v). The dynamic spinal stiffness measures are obtained during TV3 and TV9.

### Data collection, management and quality control

A customized submission, tracking and reporting web-based system was developed for the study. It is comprised of multiple sub-modules integrated into one comprehensive study management web application that includes sub-modules for computer assisted telephone interviewing, participant eligibility checking, participant tracking and report generation. The ASP. NET web application elements were programmed in C# and Structured Query Language (SQL) using Microsoft Visual Studio 2010 (Microsoft, Redmond, WA, USA) and Microsoft SQL Server Management Studio. User-friendly data entry interfaces were programmed with appropriate participant flow restrictions, validation schemes and skip patterns. The system uses a Project/Users Permissions System to control project personnel access to web modules. The web system is password-protected and uses a Microsoft SQL Server database platform to store all data.

Information is collected at every stage of recruitment, and throughout treatment and assessment so that the patient flow can be reported according to the Consolidated Standards of Reporting Trials guidelines
[63]. We collect recruitment source, total number of responses per recruitment source, the resolution of these responses (ineligible, refused or enrolled), the number of withdrawals and reason for withdrawal, and the number of participants completing the study. For each enrolled participant, we track compliance to the treatment protocol and the assessment data that were collected at each visit.

Participant self-report questionnaires and clinician-reported SM delivery records are paper-based forms with unique participant identification numbers. Study coordinators have oversight for all paper data collection forms, log each completed form into a form tracking interface of the web system and submit data forms for key-entry weekly. These forms are double key-entered by trained data entry clerks in an MS Windows program using range and validation checks to improve accuracy and are stored in locked filing cabinets. The electronic biomechanical data are stored on a password protected network file server. Data reduction is completed within 2 weeks of data collection, transferred to the data manager in Microsoft Excel workbooks, and then uploaded to Microsoft SQL Server and stored with all other project-related data.

Data management and quality control of all data are performed using SQL views, stored procedures and real-time, web-based reports. Automated reports are viewed by the data manager to determine if quality improvement actions must occur, such as improved documentation, protocol revisions or personnel retraining. Final project datasets of combined web, paper and biomechanical data are assembled by transferring data from Microsoft SQL Server to SAS System for Windows (Release 9.3, SAS Institute Inc., Cary, NC, USA). Back-up tapes of the network drive are produced nightly.

### Protection of human subjects and assessment of safety

#### Protection of human subjects

The study protocol was approved by the Palmer College of Chiropractic IRB.

#### Data and Safety Monitoring Committee (DSMC)

This trial is being monitored by an independent DSMC comprised of epidemiologists with expertise in LBP and CAM clinical trials, a biostatistician and a doctor of chiropractic. The DSMC’s role is to provide scientific and ethical oversight by evaluating the following data provided to them on a semi-annual basis: participant recruitment, accrual, and retention; adverse events (AEs); protocol deviations; data monitoring; and participant characteristics. To further monitor participant safety, serious AEs are reported to the chair of the DSMC within 5 business days. The DSMC makes recommendations to the Principal Investigator and the Office of Clinical and Regulatory Affairs at the National Center for Complementary and Alternative Medicine regarding continuation, termination, or other modifications to the study.

#### Adverse events

An IRB-approved AE grading and reporting protocol defines the process by which AEs are monitored and categorized for this study. This protocol also outlines when and how participant safety concerns are reported to the IRB, DSMC and funding agency. An AE is any untoward medical occurrence that may present itself during the conduct of the study and which may or may not have a causal relationship with the study procedures
[64]. A serious AE is defined as any adverse event resulting in any of the following outcomes: death, a life-threatening adverse experience, hospitalization or prolongation of existing hospitalization, a persistent or significant disability/incapacity, or a congenital anomaly/birth defect resulting from a pregnancy. Participants are asked about adverse experiences at each TV and instructed to contact study personnel if they experience significant pain, discomfort or distress that they believe may be associated with treatment.

### Statistical analysis

SAS System for Windows and R (http://www.r-project.org/) will be used for data analysis. Descriptive statistics of participant baseline characteristics and all measurements for each of the 3 assessment times will be calculated. The 3 different methods of collecting spinal stiffness will be compared with intraclass correlation coefficients. The general approach to data analysis will be to first summarize the variations in the physiological and kinetic measures using hierarchical linear regression models and then to use that information to determine the most appropriate statistical methods, including linear mixed regression models
[65] and conditional linear mixed regression models
[65, 66].

For Specific Aim 1, the variations in physiological measures will be summarized using a hierarchical linear regression model with a random effect for participant. If there is a non-significant random effect for participant, then this estimated random effect will be considered a sufficient summary of the physiological measures over time and linear mixed regression models will be used to examine the association between that random effect and the patient-centered outcome variables. If there is a significant random effect for participant, then there is variation in the measures over time. In this case, a linear mixed regression model with time-varying covariates will be fit to assess the association between the physiological measurements at a particular time point and patient-centered outcomes at the subsequent visit(s).

For Specific Aim 2, the variations in kinetic measures will be summarized using a hierarchical linear regression model with random effects for clinician and for participant nested within clinician. Intraclass correlation coefficients will be computed to establish if there is substantial consistency within clinician within participants and within clinician across participants and if there is sufficient variation between clinicians to allow evaluation of how variations in kinetic measures can predict patient-centered outcomes. If the random effect for participant within clinician is non-significant, or the intraclass correlation coefficient is 0.7 or higher, then the estimated random effect for clinician will be considered a sufficient summary of the delivery of care by an individual clinician. In this case, the association between this random effect and patient-centered outcomes will be evaluated using a linear mixed regression model. If there is not sufficient consistency within clinician between patients, but there is consistency within a clinician within participants, it will indicate that clinicians vary their care by participant but provide a consistent level of care across the course of treatment. In this case, the linear mixed regression model will be used to estimate the association between random effects specific to the clinician/participant combination and patient-centered outcomes. If consistency within clinicians and within participants cannot be established, this indicates substantial variation in the care provided across time by clinicians within a participant. In this case, we will fit a linear mixed regression model with time-varying covariates to assess the association between the kinetic measurements at a particular time point and patient-centered outcomes at the subsequent visit(s).

In the analysis for both specific aims 1 and 2, the complexity introduced by modeling with time-varying covariates may be better served with conditional linear mixed models. Regardless of what model is chosen, alternative models will be fit to assess the sensitivity of the statistical model to any assumptions about consistency.

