1A). During the hand palpation assessment, the participants lie face down on a custom-made chiropractic treatment table with force plates (Model 4060-NC, Bertec Inc., Columbus, OH) embedded under the cushions that support the thoracic and pelvic regions and acquire the palpatory force transmitted through the participant. The clinician applies a gentle anteriorly directed force consistent with the level typically used during examination to the vertebral levels L1 to L5. An infrared smart marker (Optotrak 3020/Certus hybrid system, Northern Digital Inc., Waterloo, Ontario, Canada) is placed on the clinician’s palpatory hand to simultaneously acquire displacement. The sampling rate for the Optotrak system is set at 100 Hz while the sampling rate for the force plates is set at 1000 Hz. No specific instruction is given to participants in terms of their breathing during the test. Figure 1B demonstrates the setup for the palpatory stiffness measurement.

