The hand-held stiffness device consists of a force transducer (Model # LC201-50, Omegadyne Inc., Sunbury, OH) and infrared smart markers for accurate force and displacement measurement. The assessment is performed with the participant lying prone on the treatment table. The examiner assesses tolerance of participants by pressing gradually up to a maximum of 80 N with the stiffness device in an anterior direction over the pre-marked spinous process of each lumbar vertebra from L1-L5. Participants inform the examiner if the pressure causes discomfort. When the maximum pressure of 80 N is reached an audible tone sounds as feedback to the examiner to stop compressing and withdraw the device. If pressure from the stiffness device causes discomfort, the test is reapplied more slowly and the participant indicates the level of pressure causing discomfort. If the tolerance test does not cause discomfort with 80 N of pressure at any vertebral level, the subsequent stiffness tests are conducted with a maximum pressure of 80 N. If the participant indicates discomfort during the tolerance test, the subsequent stiffness test is conducted at all vertebral levels using a maximum force value 10 N lower than the lowest value causing discomfort at any vertebral level during the tolerance test. If tolerance to the hand-held stiffness device is less than 60 N at any vertebral level, the hand-held stiffness test, as well as the automated stiffness test, is not performed. Both force and displacement are recorded using a Motion Monitor data acquisition workstation (Innovative Sport Training, Chicago, IL) at a sampling rate of 1000 Hz. The stiffness measures are performed by pressing anteriorly over each lumbar spinous process for 5 cycles at a rate of approximately 1 repetition per second. The participants are instructed to make a deep breath in, a deep breath out, and then inhale half way and hold their breath during which the test is performed. The average stiffness obtained over the last 4 cycles is used for analysis. Figure 
1C demonstrates the setup for the hand-held stiffness measurement.

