**Figure 1 Fig1:**
[figure not shown]
**Illustration of spinal stiffness assessment tests.** Skin marks over bony landmarks of the T11-L5 spinous processes and posterior superior iliac spine **(A)**, palpatory stiffness assessment **(B)**, stiffness assessment with a hand-held device **(C)**; and stiffness assessment with an automated device **(D)**.

The automated stiffness test consists of 1) a height-adjustable treatment table equipped with safety switches to allow either the participant or examiner to immediately lower the table thereby withdrawing from the automated stiffness device; 2) an automated stiffness device that extends and applies a designated force; and 3) a computer system to program device movement based on displacement/force data sent from the device in real-time using a custom-written program in LabVIEW with a sampling rate at 200Hz (Version 8, National Instruments Corp., Austin, TX)
[23, 58, 59]. The automated stiffness device is positioned over the spinous process nearest the most concave point of the lumbar curve while in the prone position, typically corresponding with the L3 spinous process. When the lumbar spine is not concave in shape (e.g. flat or convex lumbar spine) or the L2 or L4 level appears to be at similar height as L3, the automated stiffness device is placed over the L3 spinous process. Participants are instructed to lay prone, inhale then exhale normally, and hold their breath at the end of exhalation for approximately 10 seconds during which the automated stiffness test is performed. During the test, the actuator on the automated device advances at a rate of 2.5 mm per second. After reaching a preload force of 5 N on the target spinous process, the actuator holds the preload for one second before advancing further and applying a maximum load of 60 N. The maximum load is maintained for one second before the actuator retracts. To decrease participant’s burden in holding the breath, the initial position of the actuator is placed as close as possible to the target spinous process as long as the participants can breathe normally without pushing against the actuator. The procedure is conducted three times during each assessment with a testing trial performed prior to data collection to orient the participant to the procedure and to determine safety. The average stiffness of the three trials is used for analysis. Figure 
1D demonstrates the setup for the automated stiffness measurement.

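### The three stiffness methods are compared by intraclass correlation alone, which cannot tell an offset or scale difference between methods from failure to rank participants alike

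*Protocol article*

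**What the plan says.** The planned comparison is one sentence in the Statistical analysis section: "The 3 different methods of collecting spinal stiffness will be compared with intraclass correlation coefficients". The ICC form, spinal level, time point and any pairing are not stated.

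The section on posterior-anterior stiffness describes three different procedures:

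- **Palpation.** The force is "consistent with the level typically used during examination to the vertebral levels L1 to L5". On breathing: "No specific instruction is given to participants in terms of their breathing during the test". Force is recorded by plates under the table cushions.
- **Hand-held device.** "The stiffness measures are performed by pressing anteriorly over each lumbar spinous process for 5 cycles", at about one repetition per second, with the last four cycles averaged. Participants "inhale half way and hold their breath during which the test is performed". Force is recorded by a transducer in the device.
- **Automated device.** "The automated stiffness device is positioned over the spinous process nearest the most concave point of the lumbar curve", usually L3. Participants "hold their breath at the end of exhalation for approximately 10 seconds". The actuator advances at 2.5 mm per second to 60 N, and three trials are averaged.

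The same section names the hand-held device as the primary stiffness measure, describes the palpation versus hand-held comparison as exploring an association, and explains that the automated test began only after 20 participants had been enrolled. Its data-reduction paragraph defines stiffness as the force-displacement slope between 10 N and 60 N for palpation and the hand-held device, and says that the automated test uses the same algorithm. Under Study design, the test order is fixed: palpation, hand-held, automated.

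**The concern.** An ICC across methods is a ratio of shared variance to total variance on one common metric. Anything that shifts one method's mean (under absolute agreement) or changes its spread (under either form) lowers the ratio, even if every participant keeps the same rank. These three procedures could well differ in mean and spread for reasons unrelated to how well they order participants: breathing state, where force is sensed, how fast load is applied, which level is tested, and position in a fixed sequence.

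At stake is interpretation. The stated question for palpation and the hand-held device is whether they are associated. If the only result is a low ICC, the reader cannot tell whether the methods rank participants differently or rank them alike on different scales. The first would speak against using one in place of the other in any form; the second could be handled by calibration.

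**Working it through.** The protocol gives no figure for this comparison to reproduce. The sample of 80 carries no precision target for an ICC. The check therefore has four parts.

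**1. Conditions side by side** (section on posterior-anterior stiffness)

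| | Palpation | Hand-held | Automated |
|---|---|---|---|
| Level | L1 to L5 | L1 to L5 | one, usually L3 |
| Breathing | no instruction | held at half inhalation | held at end of exhalation |
| Force sensed | plates under cushions | transducer in device | device itself |
| Loading | usual gentle force | about 1 repetition per second, to 80 N or a reduced maximum | 2.5 mm per second, to 60 N |
| Slope window | 10 to 60 N | 10 to 60 N | same algorithm |

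Level can be matched afterwards, because palpation and hand-held readings exist at every lumbar level. Breathing, sensing site and loading rate cannot be matched; they belong to the method difference.

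**2. What an ICC does with offset and scale**

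For several methods measured on the same participants:

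- consistency ICC = mean covariance / mean variance
- absolute-agreement ICC = mean covariance / (mean variance + variance of the method means)

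All offsets and scale factors below are assumptions; none comes from the protocol.

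*Consistency 0.80, equal variances, method means in equal steps:*
- steps of 0.5 SD (variance of means 0.25): agreement = 0.8 / (0.8 + 0.2 + 0.25) = 0.64
- steps of 1 SD (variance of means 1.0): agreement = 0.8 / (0.8 + 0.2 + 1.0) = 0.40
- consistency stays at 0.80 in both cases.

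*All pairwise correlations 1.00, negligible error:*
- offsets 0, 0.5, 1 SD: agreement = 1 / 1.25 = 0.80; consistency 1.00
- offsets 0, 1, 2 SD: agreement = 1 / 2 = 0.50; consistency 1.00
- scale factors 1, 1.5, 2, no offset: mean covariance = (1.5 + 2 + 3) / 3 = 2.167; mean variance = (1 + 2.25 + 4) / 3 = 2.417; both forms = 0.90
- the same scale factors with offsets 0, 1, 2 (in SDs of the first method): agreement = 2.167 / 3.417 = 0.63; consistency 0.90.

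So the consistency form removes the offset problem and leaves a smaller scale problem. The absolute-agreement form has both.

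**3. Numbers available**

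With 80 enrolled, at most 80 − 20 = 60 participants (75%) can have all three methods, before dropout and before the tolerance rule that omits both device tests. The Sample size section gives 80 as a minimum, so 60 is the count at the planned size. Palpation versus hand-held can still use up to 80. For a two-method ICC of 0.7 (assumed), the approximate standard error is √[2(1 − r)²(1 + (k − 1)r)² / (k(k − 1)(n − 1))]. With k = 2, the full 95% interval width is about 0.22 at n = 80 and 0.26 at n = 60, a modest loss.

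**4. Load**

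The common 10 to 60 N slope answers most of the worry about different peak loads. One gap remains. The hand-held maximum is set 10 N below the lowest force causing discomfort, and the test is omitted when tolerance is below 60 N. If tolerance means the force at which discomfort occurs, discomfort at 60 to 69 N gives a maximum of 50 to 59 N, short of the upper slope point. If it means the reduced maximum, the gap does not arise. Gentle palpation is also not assured of reaching 60 N. The protocol should reconcile these statements.

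**The case against.** The strongest reply is that the sentence leaves the form open. It speaks of coefficients in the plural, and level-matched, pairwise consistency ICCs would fit it. Form and matching can properly be left to an analysis plan, which is not at hand. That stands, so the missing ICC form is not the point here. What remains is that ICC is the only kind of statistic named for the comparison, and even the consistency form mixes scale with ranking.

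Second, the same section promises descriptive statistics for all measurements, so each method's mean and spread will be visible. This helps in part. But those summaries need not refer to the same level or the same participants, and they give no paired differences.

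Third, breathing, sensor site and order are features of each method, which a method comparison should include. That is right; they need to be named when the result is interpreted, not removed.

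Several stronger readings are tempting, and the documents do not support them:

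- *The plan treats the methods as interchangeable.* This would follow fully only from a one-way or absolute-agreement ICC, and neither is specified.
- *A low ICC would misdirect the choice of device for the next trial.* No decision rule hangs on this ICC. The hand-held device is already the primary measure, and the 0.7 threshold in the same section concerns kinetic measures in Specific Aim 2.
- *Different peak loads make the readings incomparable.* The common slope window largely answers this, apart from the gap shown above.
- *The late start of the automated device, or the lack of global stiffness variation from it, is an error.* The late start is disclosed with reasons and only reduces the sample. The variation measures are expressly limited to palpation and the hand-held device.

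**Conclusion.** The concern holds in a limited form. Using ICC alone is a weak choice for three procedures that differ in level, breathing, force sensing and loading rate, and it does not directly answer the association question stated for palpation and the hand-held device. The fault applies fully to an absolute-agreement ICC; for a consistency ICC only the scale part remains.

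The size cannot be fixed from the protocol. With consistency at 0.80, the values 0.64 and 0.40 assume absolute agreement and offsets in steps of 0.5 and 1 SD. Scale factors of 1, 1.5 and 2 would lower a perfect consistency ICC only to 0.90. The comparison is descriptive and separate from the Aim 1 outcome models, so this is a worthwhile, inexpensive improvement rather than a threat to the study's main results.

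**What to change.** Replace the single sentence with a pairwise comparison along these lines: using pre-manipulation readings, each pair of methods will be compared at the lumbar level on which the automated device was placed, in participants with both readings. For each pair, report:

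- the number of participants (at the planned size, up to about 60 for pairs with the automated device and about 80 for palpation with hand-held);
- the mean difference with limits of agreement;
- a consistency ICC or a correlation, with its confidence interval.

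Participants enrolled before the automated test began have no automated level. For them, the palpation versus hand-held pair needs a stated level, for instance the level that the automated placement rule would have selected, since the most concave segment is marked on the skin during the stiffness assessment.

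Add that the differences include the differing breathing and loading conditions and the fixed test order. Reconcile the 60 N upper slope point with the reduced hand-held maximum.

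No new data are needed. The cost is a few lines of text, a little more programming, and three pairwise summaries in place of one type of coefficient.
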